## 3. Discussion

This study has two primary purposes. First, to study the effect of a preoperative aerobic exercise program with a portable upper extremity cycle ergometer on immediate postoperative mobility. Second, to investigate the additional effect of an 8-week postoperative aerobic exercise program with a portable upper extremity cycle ergometer on the walking distance at 8 weeks after surgery. This study also has a number of secondary objectives. Regarding the preoperative exercise program evaluation of the effect of the preoperative program on surgical stress (via blood lactate levels), perioperative bleeding and transfusion requirements, hemostasis factors will be evaluated, in addition to, an evaluation of the effect of the postoperative program in the short and long term: lower extremity functionality, aerobic capacity, nutritional status, hemostasis factors, mortality, rehospitalization and complications related to surgery and hospitalization (thrombotic and thromboembolic events).

Undoubtedly after a hip surgery, postoperative rehabilitation is a well-established evidence-based practice [1,58,59]. The first days after the surgery seem to be the most critical for the patient’s subsequent independence. In a recent retrospective study, early mobilization (walking >1.5 m within 72 h postoperatively) was noted to be associated with fewer postoperative complications (myocardial infarction, pneumonia, admission to the intensive care unit or nursing home) and mortality within three months [60]. This has also been indicated by the high predictive value of the Cumulated Ambulation Score (CAS) [41]. Traditionally, the rehabilitation of hip fractures is based mainly on hip muscles strengthening [61,62] and improving mobility through gait retraining and functional tasks [1,63]. However, previous studies [17,64] have established the positive effect of aerobic exercise with a nonportable arm crank ergometer on outcomes such as the maximal oxygen uptake (VO_2_max), mobility and independence (Timed Up and Go test and 6-min walking distance), functionality and quality of life of patients after a hip fracture. Similar improvements in the outcome measures have been demonstrated after total hip arthroplasty, with favorable results relative to the control group being maintained up to one year after surgery [65]. Although intensity is an important factor for exercise effectiveness, and most published exercise protocols refer to moderate-intensity continuous training for elderly individuals, moderate-intensity interval training seems sufficient for functional and metabolic improvements in older adults [66,67]. Our pilot trial has revealed that interval training may be more appropriate and feasible for this population, considering the advanced age, comorbidities and lack of exercise experience these patients have.

There is less evidence about the value of prehabilitation, which is, however, suggested as appropriate, or even necessary, both for the prevention of postoperative complications and the best outcome of surgery [68,69], as well as for the favorable cost-effectiveness it offers [70]. Based on the existing literature on both the benefits of aerobic exercise on cardiorespiratory health and functionality in patients with hip fractures [17,64], the positive regulation it brings about in biochemical markers such as hypercoagulability [22,23] and albumin [71,72], we hypothesize that a pre- and postoperative exercise program can provide a comprehensive, multidimensional and multisystemic benefit to patients after a hip fracture. Delayed surgery, beyond 48 h of admission, is a worldwide issue [73]. Although, in regional hospitals, the length of waiting time might be considered during early surgery on average [74], in major hospitals, almost one-third are delayed surgeries in Greece [75]. Therefore, considering the Greek reality where, in hospital clinics, patients’ surgeries are delayed due to a disproportion in the number of cases and staff, resulting in a possible impact on patient outcomes [76], there is an immediate need to investigate the dynamics of such a conservative intervention in biochemical markers related to morbidity and mortality.

Although postoperative (post-hospitalization) moderate-intensity aerobic exercise programs have been used in hip fracture patients and tested for safety and efficacy [17,64], these patients typically fail to incorporate the minimum weekly physical activity guidelines into their rehabilitation program, as recommended by the World Health Organization, both during their hospitalization and during their later life in the community [77,78]. To date, aerobic exercise rehabilitation programs for these patients have relied on nonportable upper extremity cycle ergometers. This implementation is a critical limiting factor in the applicability and feasibility of such programs in the real world, given that, for older adults, the inability to move outside the home is the second-most important factor for not participating in an exercise program, with the most important being a lack of interest in exercise itself [79,80]. In a recent retrospective observational study of 681 hip fracture patients, preoperative implementation of a physical therapy program of lower extremity strengthening and range of motion (in the unaffected extremity) showed a statistically significant improvement in the level of independence at discharge in comparison with the control group [81].

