## 2. Materials and Methods

### 2.1. Study Design

The study protocol has been prospectively registered in the open database for study protocols, ClinialTrials.gov (registration number: NCT05389800) [33]. The study received approval number 402/26-7-2021 from the Institutional Review Board of the “Attikon” University Hospital (1st Department of Orthopaedic Surgery, National and Kapodistrian University of Athens) 7 September 2021.

A parallel group, single-blinded, randomized controlled trial (RCT) will be conducted with two groups of hip fracture patients. The sample will be recruited from a tertiary University Hospital (1st Department of Orthopaedic Surgery, “Attikon” University Hospital, Athens, Greece). The randomization will be done at the time of admission of the patients to the emergency department (ED) and after their written informed consent form. The study protocol’s instructions will be described through an informed consent form in plain language, along with all the procedures the subjects will undergo and the risks and benefits of participation. Allocation concealment will be ensured by using sequentially numbered, opaque, sealed envelopes. The envelopes were created by a biostatistician, who will participate actively in neither the delivery of any intervention nor in the outcome measures assessment. For the preoperative program, 116 patients need to be recruited, who will be randomized with a ratio of 1:1 using the block randomization method (58 in the intervention group and 58 in the control group). Immediately after the surgery, the participants of each group will continue in the postoperative intervention program: the intervention group (IG) will continue with the exercise program three times a week for a total of 8 weeks, while the control group (CG) will not receive any intervention at any time point after surgery (Figure 1, graphic illustration).

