#### Attention Control Group

The control group will participate in a program of memory and attention activities of very low intensity with upper extremity movements using an interactive platform (Kinesthetic Multi-Sensory Games, Kinems, Greece). To maintain equal attention time with the intervention group, the program will last 20 min. There will be a simultaneous recording of the HR, while the RPE scale will be evaluated at the end of each session. For the postoperative program, no intervention will be performed beyond the standard care, such as physical therapy sessions without aerobic exercise.

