### 2.8. Statistical Analysis

#### 2.8.1. Sample Size Calculation

Power analysis for the sample size selection to highlight the preoperative program on the change in 3-day CAS was performed via the web application http://sampsize.sourceforge.net/ (accessed on 1 June 2021) for a significance level of α = 0.05 and power = 90%. The assumptions were made based on the study by Jérôme et al. [54], where m1 = 11.2 with a standard deviation = 3.1 and m2 = 13.6 with a standard deviation of 3.1. The minimal clinically important difference (MCID) between groups for the 3-day CAS was set at 2.4 units, given that the MCID for the 1-day CAS was found to be 0.8 units [39]. The ratio between groups will be 1:1. Due to factors such as in-hospital mortality, the drop-out rate is 10%. Considering the above assumptions, the minimum required sample to highlight the preoperative effectiveness of the exercise in the immediate postoperative basic mobility assessed with the 3-day CAS is set at 80 subjects (intervention group n1 = 40, control group n2 = 40).

The power analysis for sample size selection to demonstrate postoperative program change in the 6-minute walking test after program completion at eight weeks postoperatively was also performed via the web application: http://sampsize.sourceforge.net/ (accessed on 1 June 2021), with a significance level α = 0.05 and power = 90%. Based on previous studies [47,55,56], the 6MWT after a hip fracture at various time points (6 months, 20 days and one month postoperatively, respectively) varies approximately at 250 m of travel distance with a standard deviation of between 70 and 80 m. From the above-mentioned results, our assumptions for the power analysis, also assuming a clinically significant difference between the groups at 50 m, are m1 = 250 with a standard deviation = 75 and m2 = 300 with a standard deviation of 75. Considering the ratio between groups will be 1:1, the sample size is 96 patients (48 in each group).

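### The week-8 6MWT contrast estimates the combined pre- and postoperative programme; calling it the additional effect of the postoperative programme needs an unstated no-carry-over assumption

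*Protocol article*

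**What the plan says.** **Design.** Section 2.1 describes a parallel-group trial: "randomized controlled trial (RCT) will be conducted with two groups of hip fracture patients". Randomisation takes place once, on arrival in the emergency department and after consent. After surgery, "the intervention group (IG) will continue with the exercise program three times a week for a total of 8 weeks". The same section gives the other arm no study treatment once the operation is over. The Attention Control Group section agrees: memory and attention activities before surgery, and then "For the postoperative program, no intervention will be performed beyond the standard care". No pre-only arm, post-only arm or second randomisation is described.

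**Aims.** The Discussion names two primary purposes. The first is "to study the effect of a preoperative aerobic exercise program with a portable upper extremity cycle ergometer on immediate postoperative mobility". The second is "to investigate the additional effect of an 8-week postoperative aerobic exercise program with a portable upper extremity cycle ergometer", on walking distance at eight weeks. The Abstract and the end of the Introduction also speak of an added or additional effect.

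**Sample size.** Section 2.8.1 bases the 6MWT calculation on the aim "to demonstrate postoperative program change in the 6-minute walking test after program completion at eight weeks postoperatively", so it assigns the whole 50 m difference to the postoperative phase. The Discussion also lists the short- and long-term secondary outcomes (function, aerobic capacity, nutrition, haemostasis, mortality, rehospitalisation, complications) as effects of the postoperative programme.

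**The concern.** The effect named in the second aim is not the effect that the two arms differ by. At week 8 the intervention arm has had both exercise phases and the control arm neither. A positive result, reported under the stated aim, would be read as evidence that eight weeks of arm cycling after surgery adds something to the preoperative programme or works without it. The data could not tell that apart from lasting benefit of the preoperative sessions.

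This affects a primary claim. A hospital deciding whether to fund the preoperative part, the home-based part or both would take guidance from a phase-specific statement that the trial does not support. The problem lies in what the article states, not in detail left to an analysis plan: no analysis of these two arms supplies the missing comparison.

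**Working it through.** **1. The plan's own figure.** Inputs from section 2.8.1: difference 50 m, SD 75 m, alpha 0.05 (taken as two-sided, which reproduces the figure), power 90%, ratio 1:1.

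n per arm = 2 × (1.960 + 1.282)² × 75² / 50² = 2 × 10.51 × 2.25 = 47.3, rounded up to 48; total 96, as stated. The 20% increase gives 48 × 1.2 = 57.6, rounded up to 58 per arm; total 116, as stated. The arithmetic is sound. The question is which effect it powers.

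**2. Which effect the contrast measures.** Write μ(a,b) for mean week-8 6MWT, with a = 1 if preoperative exercise was given and b = 1 if postoperative exercise was given. The trial observes μ(1,1) and μ(0,0) only. Their difference splits as

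μ(1,1) − μ(0,0) = [μ(1,0) − μ(0,0)] + [μ(1,1) − μ(1,0)].

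The first bracket is preoperative carry-over to week 8. The second is the additional effect of the postoperative programme. Both need μ(1,0), which no arm provides. The second bracket equals the observed difference only if the first is zero.

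**3. Does the article support zero carry-over?** It does not state it. The Expected Outcome section predicts that the preoperative programme will speed early recovery of basic mobility. The Discussion calls the first postoperative days the most critical for later independence and cites the predictive value of the Cumulated Ambulation Score (CAS). Both point towards some carry-over.

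**4. Could the planned analyses separate the phases?** Section 2.8.2 plans two-group tests, multiple regression and repeated-measures ANOVA. Section 2.7.2 and Table 1 place the first 6MWT at week 4, after postoperative exercise has begun, so there is no 6MWT value from the start of that phase. CAS is measured after randomisation, so adjusting for it would not restore a randomised comparison.

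**5. Illustrative size.** The documents give no carry-over value; those below are assumed. The standard error at 48 per arm is 75 × √(2/48) = 15.3 m. The last column is the chance of a significant 6MWT test if the postoperative programme did nothing.

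| Assumed carry-over | Left for postoperative phase in a 50 m difference | Chance of significance from carry-over alone |
|---|---|---|
| 0 m | 50 m | 5% |
| 10 m | 40 m | about 10% |
| 25 m | 25 m | about 37% |

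**6. Does 3-day CAS isolate the preoperative phase?** Section 2.1 has the groups move into the postoperative programme immediately after surgery, and section 2.5 says that programme starts in hospital. Section 2.7.1 scores CAS on postoperative days 1, 2 and 3. On these statements the first postoperative sessions may fall inside the CAS window.

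**The case against.** **The randomised comparison is valid.** This stands. A reader might infer that the week-8 result is uninterpretable, or that the postoperative effect can never be estimated. Neither follows. The contrast is an unbiased randomised comparison of two strategies, and the Discussion itself hypothesises benefit from a pre- and postoperative programme taken together. Under negligible carry-over the postoperative effect would be identified. What fails is attribution to one phase without stating that assumption.

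**Carry-over may be small.** The planned doses differ widely. Preoperative work is 4 × 2 min twice a day, or 16 min per day; postoperative work is 8 × 2 min × 24 sessions = 384 min. With an assumed 2 to 5 preoperative days, the preoperative share is 32/416 to 80/464, about 8% to 17% of total work. This is a fair reason to doubt a large carry-over. However, share of exercise time is not share of effect, and the article's case for the preoperative programme rests on the timing of recovery, not on volume.

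**Additional may mean beyond standard care.** The arms would still differ in preoperative exercise, so the difficulty remains.

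**Unmatched contact.** A reader might add that the intervention arm has 24 supervised sessions after surgery and the control arm has none. The article openly declares standard care as the postoperative comparator and claims matched attention only for the 20-minute attention programme, which belongs to the preoperative phase. Contact time affects how the result is interpreted, but it is a separate matter and would remain even with a second randomisation.

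**Conclusion.** The point holds as one of attribution. Two arms and a single randomisation at admission estimate the week-8 effect of the combined programme against preoperative attention control followed by standard care. The additional effect of the postoperative programme follows from that only if preoperative carry-over to week 8 is nil, which the article neither states nor supports.

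The size is unknown. The split of 50 m into 50, 40 or 25 m rests wholly on the assumed carry-over of 0, 10 or 25 m. A reader might turn the last row into a claim that the postoperative effect is overstated by up to 100%; no figure in the article supports that.

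A reader might also conclude that 3-day CAS is left as the one clean test of the preoperative programme. The article does not secure this, because in-hospital postoperative exercise may overlap days 1 to 3. Nor would CAS be the only such outcome: the Discussion also lists lactate, bleeding and transfusion, and haemostasis for the preoperative phase.

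**What to change.** 1. Restate the second primary objective, its hypothesis in Expected Outcome and the 6MWT paragraph of section 2.8.1 as: the effect on 6MWT at week 8 of combined pre- and postoperative interval training versus preoperative attention control followed by standard care.
2. Delete added and additional effect in the Abstract, Introduction and Discussion.
3. Use the same combined-programme wording for the short- and long-term secondary outcomes that the Discussion assigns to the postoperative programme.
4. Reconcile sections 2.1, 2.5 and 2.7.1 on whether postoperative exercise overlaps postoperative days 1 to 3. Until then, do not describe 3-day CAS as a test of the preoperative programme alone.

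**Cost.** Patients, visits and N = 116 are unchanged. The claim becomes narrower, and because the trial is registered and ethics-approved, those records may need an amendment.

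If a phase-specific claim is essential, wording cannot supply it. A third arm with preoperative exercise only would need, on the plan's own assumptions and without multiplicity adjustment, 3 × 48 = 144 evaluable or 3 × 58 = 174 randomised patients.

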### Expected Outcome

For the preoperative exercise program, we hypothesize that it will reduce surgical stress through the body’s better response to lactate accumulation and acute physiologic effects on the patient’s hematopoietic activity. Exercise will reduce platelet hyperactivity, increase the activity of the fibrinolytic system and decrease the procoagulant factors. In this more favorable environment, the immediate postoperative restoration of basic mobility will be able to be accelerated. Regarding the postoperative exercise program, we hypothesize that the aerobic exercise program will improve lower extremity independence and functionality by maintaining or increasing the cardiopulmonary capacity, while improving the nutritional factors through post-exercise protein synthesis will contribute to this.

## Figures and Tables

**Figure 1 biomedicines-11-01263-f001:**
[figure not shown]
Graphical illustration of the study design. In the frame “outcomes”, only the first integration of the assessments and not the follow-up assessment can be seen. For example, mHHS will be assessed not only at admission (first integration as shown in the box) but also at 4, 8, 26 and 52 weeks (follow-up assessment). Accordingly, the evaluation of the basic mobility through the CAS scale will be evaluated on the first; second and third postoperative day and at 4, 8, 26 and 52 weeks postoperatively. Blood samples will be collected on the day of admission; one day before surgery; on the third postoperative day and at 1, 4, 8, 26 and 52 weeks postoperatively. Analysis of the coagulation biomarkers will be done by ROTEM. After the 8 weeks of postoperative intervention, there will be no intervention for any of the two groups. The time from admission to surgery will vary. Created with BioRender.com (accessed on 16 April 2023). Abbreviations: MIIT = Moderate Intensity Interval Training; CAS = Cumulative Ambulation Score; 6MWT = six-minute walk test; TUG = Timed-Up and Go; mHHS = modified Harris Hip Score; LEFS = Lower Extremity Functional Scale; NMS = New Mobility Score; La = Lactate concentration of capillary blood; ROTEM = rotational thromboelastometry; Hemostatic profile = tissue Plasminogen Activator (tPA); Plasminogen Activator Inhibitor-1 (PAI-1); Endogenous Thrombin Potential (ETP); Fibrinogen; D-dimers; von Willebrand factor antigen; von Willebrand factor activity; Thrombin–Antithrombin Complex (TAT); Thrombomodulin; platelet function—PFA-100; hemostatic profile using viscoelastic techniques—ROTEM; pre-op = preoperative; peri-op = perioperative; post-op = postoperative.

**Table 1 biomedicines-11-01263-t001:** Time points of the outcome measurements. In bold are the primary outcome measures for which the sample size was calculated for the effects of the preoperative and the postoperative exercise program.

Outcome Measures	1st Day of Admission	One Day before Surgery	During Surgery	Post-Op—to Discharge	4th Week Post-Op	8th Week Post-Op	26th Week Post-Op	52nd Week Post-Op
**CAS**				**1st, 2nd, 3rd post-op**	**✓**			
**6MWT**					**✓**	**✓**	**✓**	**✓**
TUG					✓	✓	✓	✓
mHHS	✓				✓	✓	✓	✓
LEFS	✓				✓	✓	✓	✓
NMS	✓							
La	✓		✓	12 h post-op				
Nutrional status	✓			3rd post-op	1st and 4th wk	✓	✓	✓
Hemostatic factors	✓			3rd post-op	1st and 4th wk	✓	✓	✓
Bleeding and transfusion needs			✓	✓				
Readmission					✓	✓	✓	✓
All-cause mortality and complications		✓			✓	✓	✓	✓

CAS = Cumulative Ambulation Score; 6MWT = six-minute walk test; TUG = Timed-Up and Go; mHHS = modified Harris Hip Score; LEFS = Lower Extremity Functional Scale; NMS = New Mobility Score; La = Lactate concentration of capillary blood; Nutritional status = Albumin and prealbumin; Hemostatic factors = tissue Plasminogen Activator (tPA); Plasminogen Activator Inhibitor-1 (PAI-1); Endogenous Thrombin Potential (ETP); Fibrinogen; D-dimers; von Willebrand factor antigen; von Willebrand factor activity; Thrombin–Antithrombin Complex (TAT); Thrombomodulin; platelet function—PFA-100; hemostatic profile using viscoelastic techniques—ROTEM; post-op = postoperative.

## Data Availability

The data of this study will be available from the corresponding author upon reasonable request. The data are not publicly available due to containing information that could compromise the privacy of the research participants.
